#### 5.1.2.3 Opt-out procedure

In the opt-out procedure, patients will indicate consent to be contacted 1 week after screening positive for a pain NRS to be administered if they do not tick a box of the screening survey to request that this should not occur. The screening form will include information about the project and that patients will be contacted at the centre or via telephone 1 week later about their pain if they do not tick the box. When the contact is made, the researcher will identify who they are, explain why they are contacting the patient and the purpose of this information, together with reassurance regarding confidentiality to ensure the participant still wishes to continue (Appendix 3). Patients will be given the opportunity to provide verbal consent to provide primary outcome data but will still have the option of refusal at that time. The opt-out procedure has been chosen because, when evaluating a health system level intervention, selection bias in the primary outcome would substantially impact on the ability to interpret the true efficacy of the intervention. The data being requested of participants is minimal and poses minimal risk to the participants. Where patients report pain  $\geq 2$  at this follow-up contact, they will be provided with contact details for their medical team to follow up if they so wish. Patients will be deemed lost to follow-up if they have not

899 provided pain NRS data of been given an alternative day/time to make contact after 3 attempts to  
900 contact on 3 consecutive days.

901

#### 902 *5.1.2.3 Verbal consent procedure*

903 Patients will be invited to give informed verbal consent to provide information for primary and  
904 secondary outcome analysis. These components will include the following:

905

- 906 1. Follow-up surveys: consent to be contacted at the centre or via telephone at intervals of 1, 2  
907 and 4 weeks to answer two questions about pain, 15 questions about quality of life and 19  
908 questions about sense of control over pain management;
- 909 2. A semi-structured interview: consent to be interviewed for up to 30 minutes about  
910 satisfaction with care for my pain and any information and resources they have been given  
911 by the service they attend.
- 912 3. Access to medical records: consent for the research team to access medical records relating  
913 to how pain has been assessed and managed and any hospitalisations they may have during  
914 my time on the study;

915

916 A researcher will use scripted wording to ensure patients' consent is informed and check  
917 understanding (Appendix 3). Verbal consent will be audio-recorded and kept on file as a record.

918

919

920

921

922 Obtaining informed verbal consent for secondary outcome evaluation in this study will be a process  
923 of information exchange between the study staff, the potential participant and any other person the  
924 potential participant believes should be included in the discussion. The participant information sheet  
925 will be used as a basis for the discussion, which will cover all procedures, benefits and burdens  
926 expected of possible during the study. The participant will be given opportunity (in time and  
927 physical capacity) to consider the study and formulate questions. Any questions will be addressed  
928 and answered fully.

929

930 Prior to study commencement, the research assistants will be trained in consent procedures for this  
931 study, with the opportunity to role play scenarios to ensure all information is fully covered. The  
932 consent form will be completed by the participant verbally rather than in writing.

933

934 .

935

936

937

938 Participants will keep a copy of the PISCF for their records.

#### 939 *5.1.2.4 Written informed consent*

940

941 In addition, patients will be given the opportunity to sign a separate, dedicated Medicare consent  
942 form giving permission for MBS and PBS data regarding their healthcare utilisation to be included  
943 in a component of the study evaluating cost-effectiveness.

944

945

### 946 **5.1.3 Unpaid Carers**

#### 947 *5.1.3.1 Identification of potential participants*

948 Patients who provide verbal informed consent to take part in one or more secondary outcome  
949 components will be asked whether they have an unpaid carer who meets eligibility criteria and  
950 might be interested in taking part. Where the answer is positive, the name, address and telephone  
951 number of the carer will be recorded and a letter and two copies of a carer-specific PISCF and  
952 reply-paid envelope posted out to the carer/or given to the participant to give to the carer and then  
953 followed up by telephone or at the centre.

#### 954 *5.1.3.2 Screening for eligibility*

955 Screening of carers will be undertaken by research assistants via discussion with the carer  
956 themselves.

#### 957 *5.1.3.3 Consent process*

958 Consent will follow the same verbal consent procedure as for patients. Carers can give consent to  
959 participate in either or both of the following components:

- 960
- 961 1. Assessment of carer experience via survey;
  - 962 2. Qualitative sub-study involving a semi-structured interview.
- 963

### 964 **5.1.4 Centre staff**

#### 965 *5.1.4.1 Identification of potential participants*

966 The majority of staff at each site will be eligible to participate. Staff will primarily be invited to  
967 participate via email circulars. The team will also raise staff awareness of the project and invite staff  
968 to participate by presenting at staff meetings.

#### 969 *5.1.4.2 Consent process*

970 A waiver on consent will be requested from the HREC to send out an email circular to staff with a  
971 Survey Monkey link (Appendix 4), inviting them to provide anonymous information about the time  
972 they have spent on cancer pain screening, assessment and management on their most recent full  
973 work day (Appendix 5). Completion of the survey will be taken as evidence of informed consent.  
974 Staff will be approached to take part in focus groups/interviews via the best local means, as advised  
975 by centre managers. It is envisaged that these means may include email circulars (see Appendix 6),  
976 leaving PISCFs in pigeon-holes and/or in the staff room as well as direct approach by a project  
977 assistant. Information about the study will include a contact number for staff to ring if they have any  
978 questions, and project staff will visit each site regularly giving staff the opportunity to approach in  
979 person. A secure ballot-style box will be left in staff rooms for staff who consent to return their  
980 completed consent forms between project team visits. Where staff are approached in person, the  
981 project assistant will begin by canvassing initial interest and, where necessary, arranging a later  
982 time to undertake the informed consent procedure at the staff member's convenience to minimize  
983 interference to work.

984

### 985 **5.1.5 Withdrawal**

986 Participants of all kinds will be free to withdraw at any time without jeopardizing their relationship  
987 with the centre or researchers. Whilst participants are not obliged to give a reason for withdrawal,  
988 where this is volunteered, the reason will be recorded so that any consistent reasons can be  
989 identified and addressed by changes to the protocol.

## 5.2 OUTCOMES AND MEASURES

The study measures are tabulated in Table 1. The study period for each patient will be 4 weeks or until death whichever is the shorter time. Validated measures are reproduced in Appendix 7.

### 5.2.1 Primary outcome

The primary outcome will be the probability that patients screened as having moderate-severe ( $\geq 5$ ) worst pain will experience a clinically important improvement 1 week later, as measured by 30% on a 0-10 numerical rating scale (NRS).

#### Rationale:

- One week following positive screen is considered sufficient time to allow comprehensive assessments to have been conducted and any new treatment regimens to have become established.
- The past 24 hours has been chosen as a recall period balancing the need to avoid recall bias whilst sampling a representative time window.
- The NRS is the optimal brief measure of pain severity on the basis of compliance rates, responsiveness, ease of use and applicability (46). The NRS is also the preferred response option of the most widely used and validated multi-dimensional pain scales (e.g. Brief Pain Inventory (47)).
- A threshold of 5 on the 0-10 NRS has become established for moderate cancer pain (48), and patients with pain of this magnitude form the focus of the primary endpoint because of the added urgency of reducing pain when it is moderate to severe versus mild.
- Thirty percent has been selected based on recommendations for pain trials by the US Food and Drug Administration and takes into account research evidence that the number of points needed for a minimally important difference (MID) varies according to the baseline score (49).

### 5.2.2 Table 1: Patient and carer measures

|                                             | Screening | Following consent | Weeks 1, 2 & 4 | Exit (after Week 4) |
|---------------------------------------------|-----------|-------------------|----------------|---------------------|
| Medical file review                  |           |                   |                |                     |
| DOB                                         |           | *                 |                |                     |
| Gender                                      |           | *                 |                |                     |
| Language spoken at home                     |           | *                 |                |                     |
| Aboriginal or Torres Strait Islander status |           | *                 |                |                     |
| Diagnoses (cancer and other)                |           | *                 |                |                     |
| AKPS/ECOG                                   |           |                   |                | *                   |
| Analgesic use                               |           |                   |                | *                   |
| Patient measures                     |           |                   |                |                     |
| Pain NRS                                    | *         |                   | *              |                     |
| EORTC QLQ-C15 Pal + 5 items                 |           |                   | *              |                     |
| heiQ                                        |           |                   | *              |                     |
| Availability of primary carer               |           | *                 |                |                     |
| Pain assessment and management audit        |           |                   |                | *                   |
| Carer measure                        |           |                   |                |                     |
| CES                                         |           |                   | Wks 2 & 4      |                     |
| Medicare data                        |           |                   |                | *                   |

AKPS = Australian Karnofsky Performance Scale; CES = Carer Experience Scale; DOB = date of birth; ECOG = Eastern Cooperative Oncology Group Performance Status; EORTC QLQ-C15 Pal = European Organisation for the Research and Treatment of Cancer Quality of Life Questionnaire - Palliative Care; heiQ = Health Education Impact Questionnaire; NRS = numerical rating scale

## 5.2.3 Secondary outcomes

### 5.2.3.1 Patient pain

Secondary outcomes will relate to the potential for the intervention versus usual care arm to result in the following:

1. Increase in mean reduction for worst pain severity in patients with clinically significant ( $\geq 2$ ) and moderate-severe ( $\geq 5$ ) worst pain from screening to 1 week later by half a standard deviation (0.5 SD). A MID will be assumed to be 0.5 standard deviation (SD), which is an established rule of thumb for patient reported outcomes (50).
2. Decrease in mean scores for worst and average pain across all screenings to give a population measure of effect. As for the primary outcome, the MID will be considered to be a 0.5 SD difference between control and intervention arms.

### 5.2.3.2 Patient quality of life

Patient QOL will be measured at 1, 2 and 4 weeks using the EORTC QLQ C15-PAL, a short-form of the EORTC QLQ-C30, which is perhaps the most widely used cancer-specific QOL measure (1, 51). The QLQ C15-PAL includes 15 items to reduce burden and focus on issues most relevant to people with advanced cancer. It provides scores for global QOL, physical functioning, psychological functioning, and symptoms that include fatigue, nausea and vomiting, dyspnea, insomnia, appetite loss and constipation. Importantly for this study, it also provides a score for pain interference and uses a recall period of the past week - both features will complement the pain NRSs which focus on pain severity over the past 24 hours. In this study, 5 additional items from the QLQ-C30 will be added to the C15-PAL at every administration to enable cost-utility evaluation using the the QLQ-Utility measure (53) (see below). These items assess physical functioning, role functioning, social functioning (2 items) and diarrhea, and thus also provide useful information for clinical management.

As for pain outcomes, the MID will be considered to be a 0.5 SD difference between control and intervention arms. This offers a convenient single estimate that approximates to scale-specific MIDs for deterioration and improvement developed for the QLQ C15-PAL (52).

### 5.2.3.3 Patient empowerment

The Health Education Impact Questionnaire (heiQ) will be administered at weeks 1, 2 and 4 to evaluate patient empowerment. A version of the heiQ developed in Australia specifically for cancer will be used that includes scales measuring Health service navigation, Constructive attitudes and approaches and Skill and technique acquisition (2). As well as offering an index of self-reported self-management efficacy, it is hypothesised that patient empowerment may have a direct impact on pain experience itself (29).

### 5.2.3.4 Carer experience

The Carer Experience Scale (CES) will be administered at weeks 2 and 4 to evaluate the intervention effect on unpaid carers in terms of their relationship with patients, support received and ability to carry on with their own lives (3). As for pain and QOL outcomes, the MID will be considered to be a 0.5 SD difference between control and intervention arms.

1001/ 4th September, 2018

### 1066 5.2.3.5 Cost-effectiveness

1067

1068 A cost-effectiveness analysis will evaluate the incremental costs and consequences of the  
1069 implementation strategies relative to usual care. Patient outcomes will include response at the end  
1070 of Week 1 (response is defined as a clinically important improvement of 30% on a 0-10 NRS 1  
1071 week post-screening for those with moderate-severe ( $\geq 5$ ) worst pain) for the primary cost-  
1072 effectiveness analysis and quality adjusted life years (QALYs) based on utility scores from the  
1073 EORTC QLQ-C15-PAL and 5 additional items from the QLQ-C30 (mapped from QLQ-Utility  
1074 (53)) and index values for carers using the CES for a modelled cost-utility analysis. Survey  
1075 responses will be linked to health service utilisation data accessed through the Centre for Health  
1076 Record Linkage and from Commonwealth datasets (Medicare; PBS) and hospital records. Variables  
1077 will include: ARDRG code; number of hospitalisations; length of hospital stays; number of  
1078 emergency department, outpatient, psychology/psychiatry and GP visits; health insurance status;  
1079 medication usage. Costs of the intervention will relate to the screening systems implemented at each  
1080 centre, materials for training and the manual, and staff time spent on attending training and  
1081 screening, assessing and managing cancer pain (see staff-level process measures below).

1082

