## **Control and intervention arms**

### **Control arm**

Whilst in the control arm, participating centres will be provided with an electronic or paper-based system for screening patients for worst and average pain severity via a 0-10 numerical rating scale (NRS). Centres that are already using a different tool for screening symptoms will continue to use the same tool where this is preferred, with addition of screening items for pain as necessary. Screening tools and patient-held resources will be translated to support communication by non-English speaking patients, who are at special risk for poor outcomes. Staff at the centre will be at liberty to use the pain screening data in any way they wish.

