### 667 **3.7 Blinding**

668 The nature of the intervention in this study renders blinding of health professionals impractical.  
669 Information and consent forms for patients will provide only general information about the aims of  
670 the study (i.e. that it will compare different approaches to cancer pain management) rather than the  
671 specifics of the design and intervention (see Appendix 2). Health professionals will be asked not to  
672 discuss the study design or current arm at their centre with patients and carers.

673  
674 Previous experience of cluster RCTs by the current team also suggests that attempts to blind  
675 research assistants collecting data will be impractical. Instead, attention will be paid to research  
676 assistant training and standardization of data collection as ways to limit the potential for bias.

677  
678 Personnel conducting analyses will be blinded to centre allocation.

679

680 **4.0 Control and intervention arms**

681

682 **4.1 Description**

683 Each participating centre will first be in the control arm and then transition to the intervention arm,  
684 defined as follows.

685 **4.1.1 Control arm**

686 Management, staff and patients at participating centres will be made aware of the Australian  
687 guidelines on the Cancer Council Australia Cancer Guideline Wiki and the study’s aim to test  
688 implementation of these. Where an existing screening system is not already in place, centres will be  
689 equipped with a system for symptom screening and providing reports for treating clinicians to  
690 consider during the consultation. Screening measures will be made available in Chinese, Italian,  
691 Greek, Vietnamese and Arabic, which are the languages spoken in Australia most commonly  
692 associated with poor English proficiency (43). Centres will otherwise provide care to patients with  
693 cancer pain according to local practice and will not be given training or strategies to support  
694 implementation of the screening system or guidelines.

695 **4.1.2 Intervention arm**

696 At the beginning of a *training phase*, two ‘clinical change champions’ will be identified at each site  
697 to take a leading role in administering the intervention with support from the project team. Two are  
698 needed to cover for periods of absence by one of the champions. Selection of clinical champions  
699 will be conducted in partnership with managers at each centre. Champions can be of any discipline  

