### 1242 **5.5.3 Cost-effectiveness analysis**

1243 The primary outcome for cost-effectiveness analysis will be the incremental cost per additional  
1244 responder at the end of Week 1 (response is defined as a clinically important improvement of 30%  
1245 on a 0-10 NRS 1 week post-screening for those with moderate-severe ( $\geq 5$ ) worst pain). Quality of  
1246 life data collected at weeks 1, 2 and 4 will be used to conduct a modelled cost-utility analysis. As  
1247 economic data may be skewed, confidence intervals will be estimated with bootstrap methods (6).  
1248 Sensitivity analysis will examine the effect of assumptions and determine which cost components  
1249 drive the results.

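### The cost list for the intervention includes screening that the control phase also has; unless the control phase is costed the same way, cost per additional responder is overstated.

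*Protocol*

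**What the plan says.** Section 5.2.3.5 of the protocol sets the economic contrast: "A cost-effectiveness analysis will evaluate the incremental costs and consequences of the" "implementation strategies relative to usual care". Section 5.5.3 fixes the main measure: "The primary outcome for cost-effectiveness analysis will be the incremental cost per additional" responder at the end of Week 1.

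The cost list is also in 5.2.3.5. It begins "Costs of the intervention will relate to the screening systems implemented at each" centre, adds training materials and the manual, and ends with staff time for attending training and for "screening, assessing and managing cancer pain (see staff-level process measures below").

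The control arm is described in two places. The Trial Summary says: "Whilst in the control arm, participating centres will be provided with an electronic or paper-based system for screening patients". Section 4.1.1 says that centres without a system of their own will be "equipped with a system for symptom screening and providing reports for treating clinicians to" use in the consultation. Centres with a working tool may keep it: "Centres that are already using a different tool for screening symptoms will continue to use the same tool where this is preferred". Section 4.1.1 also makes control centres aware of the guidelines, but withholds training and strategies that would support the screening system or the guidelines.

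The protocol is not uniform on where screening belongs. The four implementation strategies listed for the intervention arm in the Trial Summary do not include it. Section 1.3 names screening, with the guidelines, as being evaluated alongside those four, and Appendix 1 lists an e-screening system among the system-level strategies.

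**The concern.** Every centre starts in the control phase, so screening is running before any centre crosses over. Patients in both arms reach the primary outcome only through a screening score of 5 or more. The cost list nevertheless labels the screening system and screening time as costs of the intervention. No cost list is given for the control phase, and sections 5.2.3.5 and 5.2.4.3 and Appendix 5 do not say in which phase the staff-time survey runs.

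Taken literally, this charges to one arm a cost that both arms bear. The effect of having screening in place is in both arms and does not add to the responder difference. The ratio would therefore be biased against the package. Section 1.4 makes free national release conditional on the strategies proving cost-effective, so the direction matters.

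Calling the comparator usual care adds to the difficulty. What the trial compares against is screening with clinician reports plus awareness of the guidelines. No arm lacks screening, so the ratio cannot inform a service deciding whether to start screening.

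**Working it through.** The protocol states no unit cost, responder rate or cost-effectiveness ratio, so there is no figure to reproduce. The check is algebraic.

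**Quantities, per patient** (none has a value in the protocol; all numbers below are assumed):

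- S: screening cost at the level already present in the control phase (system and staff time)
- I: other implementation cost
- H: downstream cost difference, intervention minus control
- d: difference in response proportion, taken as positive

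**Formulas**

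- List applied as written, control phase not costed: (S + I + H)/d
- Control phase costed the same way: (S + I + H − S)/d = (I + H)/d
- Excess: S/d

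**Absolute size**

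| S (dollars) | d = 0.20 | d = 0.10 |
|---|---|---|
| 20 | 20/0.20 = 100 | 20/0.10 = 200 |
| 50 | 50/0.20 = 250 | 50/0.10 = 500 |

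**Relative size.** With I = 1 and H = 0, the two ratios stand as (1 + S)/1 at any d. At d = 0.10:

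| S as a share of I | As written | Differenced | Factor |
|---|---|---|---|
| 0.10 | 11.0 | 10.0 | 1.10 |
| 0.25 | 12.5 | 10.0 | 1.25 |
| 0.50 | 15.0 | 10.0 | 1.50 |
| 1.00 | 20.0 | 10.0 | 2.00 |

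**Sign.** With H = −1.2, I = 1 and d = 0.10, the differenced ratio is (1 − 1.2)/0.10 = −2.0, a saving. With S = 0.25 charged to the intervention only, it is (0.25 + 1 − 1.2)/0.10 = +0.5, a cost.

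**Screening time that differs between phases.** If screening takes 1 unit of staff time in control and 1.5 in intervention, the list as written charges 1.5, the proper increment is 1.5 − 1 = 0.5, and the excess is 1. Only the control-level part is wrongly charged.

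**Centres that keep their own tool.** If k of the 8 planned centres need a new system, enrolment per centre is equal and the others have no system cost, the average system cost is scaled by k/8: 0 for k = 0, 0.25 for k = 2, 0.5 for k = 4 and 1 for k = 8. The protocol does not give k.

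**The case against.** The strongest reply is that the analysis is declared incremental in both 5.2.3.5 and 5.5.3. An incremental analysis subtracts control costs, and if control-phase screening is costed, the excess is zero. The sentence on costs may be only a list of resource items to be measured and then differenced. The list supports this reading itself: it includes time spent assessing and managing pain, which control centres also do under local practice and which could not sensibly be charged to one arm. The survey is not confined to the intervention phase either; its timing is simply not stated. This stands, and it makes the bias conditional.

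Two further points also stand. Centres that keep an existing tool may have almost no new system cost. And screening activity is not identical in the two phases: section 4.1.2 trains champions in using and trouble-shooting the system and monitors how results reach clinicians. Extra screening time that follows from this is a true incremental cost with a possible matching effect. A reader might infer that all screening cost is non-incremental and that its whole effect cancels; the protocol does not support that.

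The planned sensitivity analysis on cost components could show that screening is a large item, but it would not correct an allocation to the wrong arm. Nor does the word incremental remove the conflict: the items are headed as costs of the intervention, and nothing says that they are counted in the control phase. The objection about the usual-care label is partly fair, since section 4.1.1 defines the control arm openly, but the economic sections should point to that definition.

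**Conclusion.** The cost list in 5.2.3.5 conflicts with the control arm in 4.1.1 and should be reconciled with it. Applied as written, without costing the control phase in the same way, it overstates the cost per additional responder by S/d. With no downstream cost difference, that is a factor of 1.10 to 2.00 when shared screening cost is 10% to 100% of other implementation cost. Those shares, the dollar figures and the response differences are assumptions; the protocol gives none, so the real size is unknown. It is zero if control-phase screening is costed equally.

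A reader might conclude that the ratio will certainly be overstated. The protocol does not go that far: it calls the analysis incremental and is silent on how control-phase screening is costed. The conflict in the text is clear; the resulting bias is a conditional risk to the main economic measure, not to the primary clinical outcome.

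**What to change.** In 5.2.3.5, reconcile the cost list with 4.1.1:

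- Charge screening-system costs equally to both phases, or leave them out of the incremental cost.
- Measure staff time on screening, assessment and management with the existing anonymous survey in both the control and the intervention phase, and enter only the difference. Extra screening time caused by training then still counts.
- In 5.2.3.5 and 5.5.3, describe the comparator as the control arm of 4.1.1: screening with clinician reports and guideline awareness.
- Show any comparison with a service that does not screen only as a separate, labelled scenario, since the trial has no such arm.

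The cost is some rewording and sending an existing short survey in both phases, with no new patients or patient procedures. Timing matters for the survey: it asks about the most recent completed working day, so control-phase time cannot be collected once a centre has crossed over. For any centre where that has already happened, control-phase time would have to be a stated assumption with a range.
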